#### General outcomes

Quality of Life will be measured using the EQ-5D, both the descriptive index and EQ-VAS [51]. The EQ-5D value set that has been validated for the Singapore population using a time trade-off method and was used to calculate utility values [65]. It will also be used in the computation for Quality of Life Years (QALYs) and eventual cost-effectiveness.

Analgesia consumption will be measured using the Cumulative Analgesia Consumption Scale (CACS) which measures both the quantity and potency of the analgesia based on WHO analgesia ladder over a 1 week period [57].

Global perceived effect (GPE) [53] will be assessed with the question: With respect to your knee, how would you describe yourself now compared to before the treatment?? Answered on a seven-point Likert scale ranging from ‘Improved, an important improvement’ to ‘Worse, an important worsening’. Satisfaction with current knee function will be assessed by the Patient Acceptable Symptom State (PASS) [54] using the question: “When you think of your knee function, will you consider your current condition as satisfying? Answered by ‘yes’ or ‘no’. Participants not satisfied with current knee function will be asked to complete a second single-item question, relating to treatment failure (TF) at the 12-month follow-up: ‘Would you consider your current state as being so unsatisfactory that you think the treatment has failed?’. Answered by ‘yes’ or ‘no’.

Any adverse events (AE) and serious adverse events (SAE) will be collected during all follow-up visits using open-probe questioning to ensure all AE are recorded. SAE will be defined as any AE that results in hospitalization or is life-threatening. Participation in the trial for the subject will cease if a SAE occurs. Undergoing an indicated surgical procedure such as a knee arthroplasty for knee OA due to failure of non-surgical treatment will not be considered an AE. In the event of more than 3 SAE, decision to stop the trial will be considered however the final decision will be made by the Principal Investigator (PI) in conjunction with the ethics and clinical board. Provision for post-trial care and compensation will be made for subjects who suffer harm during the course of the trial.

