### Analysis plan

The primary endpoint in this study is KOOS_4_ at 12-month follow-up. Results will be analysed by intention-to-treat (ITT) principle. However, data will also be analysed by per-protocol (PP) approach to account for protocol violations such as patients who were deemed not compliant to treatment or patients who underwent a surgical procedure of the knee due to treatment failure during the course of the study.

Descriptive frequency analysis will be used for baseline characteristics. For continuous variables, the mean and standard deviation will be reported and for categorical variables, the frequencies and percentages will be reported. Between-group comparisons of change from baseline to 1-year follow-up in the primary and secondary continuous outcomes will be analysed using a generalized linear mixed model (GLMM). Testing for normality of distributions of outcomes will be based both on the Shapiro-Wilks test and a visual analysis of the histogram plot. Categorical secondary outcomes will be analysed using the ordinal logistic regression function under GLMM. A two-sided *p*-value less than 0.05 will be considered as statistical significance. An analysis will be done on the nature of the missing data to determine if the data was missing at random or a systemic bias was present resulting the missing data.

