### Cost estimation and outcome measurement

Cost data will be collected via hospital administrative databases and patient-reported questionnaires to estimate direct medical, direct non-medical and indirect costs. Indirect costs include health-related productivity loss due to knee OA [70] from absenteeism and presenteeism, measured with the Work Productivity and Activity Impairment Questionnaire (WPAI) [71]. The scope of the cost data collection was based on the validated OA Cost and Consequences Questionnaire (OCC-Q) [72] and adapted to the Singapore context to ensure that all relevant sources of cost were collected. The cost questionnaire used can be found in Additional file 3. Cost data will be collected at 3 monthly intervals till 1-year follow-up.

The primary measure of health benefit will be Quality of Life Years (QALYs) measured using the EQ-5D [51]. The incremental cost-effectiveness ratio (ICER) over the trial period of this multidisciplinary non-surgical community-based program for knee OA compared to usual care will be determined.

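### Read as written, the rule that an SAE ends trial participation stops collection of 12-month KOOS4, EQ-5D and questionnaire cost data after a post-randomisation health event

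*Protocol article*

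**What the plan says.** The rule is in the protocol article under General outcomes, in the paragraph on adverse events: "Participation in the trial for the subject will cease if a SAE occurs". The sentence before it gives the definition: "SAE will be defined as any AE that results in hospitalization or is life-threatening". No relation to the intervention is required. The same paragraph makes one exception: an indicated surgical procedure, with knee arthroplasty as the example, "due to failure of non-surgical treatment will not be considered an AE". Such surgery therefore does not trigger the rule.

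The Analysis plan states "The primary endpoint in this study is KOOS_4_ at 12-month follow-up" and "Results will be analysed by intention-to-treat (ITT) principle". Change from baseline to one year is compared with a generalized linear mixed model. On missing values it says: "An analysis will be done on the nature of the missing data to determine if the data was missing at random or a systemic bias". Outcomes are scheduled at baseline and at 3, 6 and 12 months (Outcomes).

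The economic evaluation uses EQ-5D QALYs as its measure of benefit and states: "Cost data will be collected at 3 monthly intervals till 1-year follow-up". Costs come from hospital administrative databases and from patient questionnaires (Cost estimation and outcome measurement).

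No section says that outcome, safety or cost collection continues after an SAE.

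**The concern.** Intention to treat needs more than analysis by allocated arm. It also needs an effort to measure the outcome in everyone randomised, whatever happens to them later. A rule that ends trial participation at a health event makes later outcomes missing by plan, for a reason likely to be related to the outcome itself.

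Three results are exposed:

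- **The primary comparison.** The 12-month KOOS4 is not measured in patients whose participation ended earlier. If SAEs are more frequent in one arm, or leave patients worse off in one arm than in the other, the comparison of observed values is distorted.
- **The economic evaluation.** EQ-5D and questionnaire costs stop at the event that is likely to drive utility loss and resource use. A few hospitalised patients can carry much of the cost in a trial of 100.
- **Safety.** Adverse events are collected at follow-up visits, so patients who have had an SAE would no longer be observed for further events.

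**Working it through.** **1. What the rule applies to.** Three features of the article favour reading it as the end of follow-up and not only of treatment.

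- It names the trial, and it applies to both arms. Usual care is a physiotherapy referral with sessions at the discretion of patient and physiotherapist, so there is no trial programme in that arm to leave.
- The programme lasts 12 weeks and follow-up lasts 12 months. After an SAE in months 4 to 12, little is left to stop beyond one support session and optional group exercise. The main effect is then on data.
- Knee surgery after treatment failure is handled differently. It is not an adverse event, and the Analysis plan deals with it through a per-protocol analysis alongside intention to treat. The protocol thus has a way to handle a post-randomisation event without ending participation, and does not use it for SAEs.

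**2. The plan's own sample size.** Inputs from Sample size calculation: difference 10, SD 14, two-sided alpha 0.05, power 90%, 20% missing, 100 recruited.

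- n per arm = 2 × (1.960 + 1.282)² × 14² / 10² ≈ 41.2, which rounds up to 42. The article gives 41.
- Inflation of 82 for 20% loss: 82 / 0.8 = 102.5, so 103; by multiplication, 82 × 1.2 = 98.4, so 99. The article gives 100.

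The stated figures reproduce closely, and this point does not depend on them.

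**3. Power.** With 100 recruited and 20% lost, 40 per arm remain. The standard error is 14 × √(2/40) = 3.13, and power by the normal approximation is 0.891. SAE losses inside the 20% leave this unchanged. If they came on top of the 20% (assumed shares):

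| SAE share | Patients per arm | Power |
|---|---|---|
| 3% | 38.5 | 0.880 |
| 5% | 37.5 | 0.871 |
| 10% | 35 | 0.848 |
| 20% | 30 | 0.790 |

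**4. Bias in KOOS4.** Let f1 and f0 be the shares of each arm whose 12-month value is lost through the rule, and D the number of points by which those patients would have scored below the others. If the others have mean m, the full arm mean is m − f × D, while the observed mean is m. An arm therefore looks too good by f × D, and the difference between arms is shifted by D × (f1 − f0), in favour of the arm with more SAEs. The article gives none of these quantities, so all values below are assumptions.

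| D (points) | SAE share, one arm | SAE share, other arm | Shift (points) |
|---|---|---|---|
| 10 | 15% | 5% | 10 × 0.10 = 1.0 |
| 15 | 10% | 5% | 15 × 0.05 = 0.75 |
| 20 | 15% | 5% | 20 × 0.10 = 2.0 |
| 15 | 10% | 10% | 0 |

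The formula uses observed 12-month values only and takes D as equal in both arms. It gives no credit for what a mixed model recovers from earlier visits.

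**The case against.** The other side has a good deal to say, and most of it limits the size of the point.

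- **Not every hospitalisation triggers the rule.** Indicated surgery such as knee arthroplasty is exempt. It is a foreseeable reason for admission here, and closely tied to KOOS4. This stands.
- **Patients need not leave the primary analysis.** A reader might infer that the sickest patients drop out of it, or that the rule flatly contradicts intention to treat. The article does not support that. A mixed model can keep these patients in their allocated arm using visits before the SAE, under missing at random. What remains is that the 12-month value is missing by rule, and missing at random is doubtful when the loss follows an acute health event. The planned check on missingness can describe the loss but cannot recover the data.
- **The loss is not one for one.** A reader might assume that 5 to 15 hospitalised patients in 100 would use up 5 to 15 of the 20 losses allowed for. SAEs are collected at follow-up visits, so one occurring after month 6 may first be recorded at the 12-month visit, when KOOS4 and EQ-5D are also taken. Using the allowance is in any case not a harm in itself.
- **Costs are not all lost.** A reader might infer that the admission and everything after it vanish from the costing. The article nowhere says that hospital-database costs are discarded. Questionnaire costs and EQ-5D after the event are what is at risk.
- **The bias is assumed and modest.** One point needs a threefold imbalance and a 10-point deficit, and compares with a target of 10 and a standard error of about 3.1. Rates of 5% to 15% would also mean more than 3 SAEs, at which the protocol would consider stopping the trial. That limits how far such rates fit the plan, but it does not settle what happens to data after each SAE.
- **The article is condensed.** It does not literally say that data collection stops, and the full protocol may provide for it. That lowers certainty about practice, but the sentence is a stated rule and its plain meaning is the end of trial participation.

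**Conclusion.** The point holds as an inconsistency in a stated rule. Ending trial participation after an SAE, with no provision for continued follow-up, makes later KOOS4, EQ-5D, safety and questionnaire cost data missing because of a post-randomisation health event. That undercuts the 12-month intention-to-treat comparison and the one-year QALY and cost evaluation.

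Its size cannot be fixed from the article, because no SAE rate is given. Under the assumptions shown, the shift in KOOS4 ranges from zero with equal shares to 2 points, with about 1 point for a 10-point deficit and 15% against 5%. The issue is bias rather than power. The economic evaluation is probably the more exposed part, but the article gives no figures from which to quantify that.

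**What to change.** Reconcile General outcomes, the Analysis plan and Cost estimation and outcome measurement by separating two things: the end of participation in the programme and the end of follow-up. State that patients with an SAE stay in follow-up for KOOS4, EQ-5D, safety and cost data at all remaining visits unless they withdraw consent, and that they are analysed as randomised. Whether the programme continues after an SAE is a clinical decision and is not addressed here.

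The change takes about one sentence in the protocol, with matching consent wording. The visits are already scheduled and the sample size does not change. The cost is some effort to follow patients after an SAE.

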#### Compliance and adherence

Compliance and adherence are key aspects in any exercises-based intervention for MSK conditions and having compliance measures allows for a more accurate interpretation of the results and form a significant part of the process evaluation [66]. Unfortunately, there is no specific measure for exercise adherence that has been proven to be high quality, relevant and acceptable [67]. In order to give a holistic picture to adherence, the Sports Injury Rehabilitation Adherence Scale (SIRAS) [55] will provide the healthcare providers perspective while a self-administered questionnaire for patients has been designed to obtain patient’s input (Additional file 2). SIRAS is a 3-item instrument that assesses patient’s intensity to exercise, the extent to which instructions were followed and receptiveness to change during each rehabilitation session. SIRAS will be done after each physiotherapy session and the exercise adherence questionnaire will be done at 3, 6 and 12 months. These adherence measures will only be performed in the intervention arm patients due to the variability of treatment delivery in the usual care arm. Non-compliance will be defined as less than 75% attendance of the prescribed treatment in the intervention arm. For usual care, the number of physiotherapy sessions will be at the discretion of the patient; thus, no non-compliance cut off limit will be set.

### Sample size calculation

The sample size needed to detect a 10-point difference between the intervention arm and usual care arm in KOOS_4_ was 41 patients in each arm based on a power of 90%, *p*-value of 0.05 (two-sided) and a standard deviation of 14. The anticipated population KOOS_4_ and standard deviations were based on the initial pilot study [25] done and the minimally clinically important difference on 10-points (MCID) for KOOS [24]. In order to account for a missing data rate of 20%, 100 patients will be recruited for the study.

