### Randomization and concealment of allocation

Patients who consent to participate will be randomized (1:1 allocation ratio) between the intervention and usual care using a stratified permuted block randomization method using block sizes of 4,6 and 8. Stratification is based on gender to ensure equal distribution in both groups. The allocation sequence is generated by an independent statistician a priori and will be kept concealed from the study team. Randomization will be done using the REDCap randomization module based on the allocation sequence and allocation will be locked once assigned. Randomization and intervention allocation will only be performed by the study team after the patient is counselled fully about the study and provides informed consent.

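### With 20% missing data, 100 recruits leave 80 patients, two short of the 82 the protocol requires; a small shortfall that restating the figures corrects

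*Protocol article*

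**What the plan says.** All the figures are in the protocol article, under Sample size calculation, apart from the allocation ratio.

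- Target effect: "The sample size needed to detect a 10-point difference between the intervention arm and usual care arm" on KOOS4.
- Required number: this "was 41 patients in each arm", "based on a power of 90" per cent, with a two-sided 0.05 level and "a standard deviation of 14".
- Allowance for missing data: "In order to account for a missing data rate of 20%, 100 patients will be recruited for the study".
- Allocation, under Randomization and concealment of allocation: patients "will be randomized (1:1 allocation ratio) between the intervention and usual care".

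The section names neither the test behind the 41 nor the formula that takes 82 to 100. It attributes the SD to the pilot study and prints it as a whole number. The Analysis plan section sets the primary endpoint at 12 months and analyses change from baseline with a generalized linear mixed model under intention to treat.

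**The concern.** The sample size section makes two linked statements: 41 evaluable patients per arm give 90% power, and recruiting 100 protects that number against 20% missing data. The second fails by simple subtraction, because 20% off 100 leaves 80 and the requirement is 82. The first is also slightly optimistic on the printed inputs. Both differences point the same way.

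What is at stake is the accuracy of a stated design property. A reader will take 90% power at 20% attrition as what the trial offers, and the abstract repeats the total of 100. If attrition does reach 20%, the final report would be citing a power that its own inputs do not support.

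**Working it through.** **Inputs** (protocol article): difference δ = 10; SD σ = 14; two-sided α = 0.05; power 90%; 1:1 allocation; missing data 20%; 100 recruited.

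**1. Reproduce the plan's number per arm.**
Normal formula: n = 2 × (z₀.₉₇₅ + z₀.₉₀)² × (σ/δ)² = 2 × (1.960 + 1.2816)² × (14/10)² = 41.19, which rounds up to 42.
Two-sample t-test (noncentral t): n = 42.17, which rounds up to 43.
The plan's 41 is therefore recovered to within 0.2 of a patient by the normal formula. A one-sided test would give 34, so the two-sided reading is the right one.

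**2. How sensitive is 41 to the printed SD?**
An SD of 13.96, which would print as 14, gives 2 × (1.960 + 1.2816)² × (13.96/10)² = 40.95 by the normal formula, and this rounds up to 41. By the t-test, an SD of 13.75 gives 40.72, again 41. The printed inputs do not quite yield 41, but an unrounded SD slightly below 14 would.

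**3. Apply the missing-data allowance.**
Retained at 20% missing: 100 × (1 − 0.20) = 80, or 40 per arm. Required: 2 × 41 = 82. Shortfall: 2.
Largest missing rate at which 82 remain: 1 − 82/100 = 18%.
Recruits needed for 82 at 20% missing: 82/0.8 = 102.5, so 103.

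**4. Power for a 10-point difference, SD 14, completers only.**

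| Per arm | Normal | t-test |
|---|---|---|
| 40 | 89.1% | 88.4% |
| 41 | 89.9% | 89.2% |
| 42 | 90.5% | 89.9% |
| 43 | 91.2% | 90.6% |

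Worked example for 40 per arm, normal: 10 / (14 × √(2/40)) = 3.194; 3.194 − 1.960 = 1.234; Φ(1.234) = 89.1%.

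**5. Difference detectable with 90% power at 40 per arm.**
Normal: (1.960 + 1.2816) × 14 × √(2/40) = 10.1 points. t-test: 10.3 points.

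**6. Missing rate up to which 100 recruits keep 90% power.**
Normal (42 per arm): 1 − 84/100 = 16%. t-test (43 per arm): 1 − 86/100 = 14%.

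**The case against.** The strongest reply is that nothing of substance is lost. Power at 40 per arm is 0.9 (normal) to 1.6 (t-test) points below 90%, the stated 41 gives 89.9% by the normal formula, and 100 recruits is within 3% of 103. This stands as a statement of size. It does not make the sentence about 20% missing data correct, because that sentence fails against the plan's own 82 whatever test is used.

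A second reply is that a completers-only comparison is not the planned analysis. Outcomes are collected at baseline, 3, 6 and 12 months, and a mixed model can draw on partial follow-up, so a patient missing at 12 months need not contribute nothing. This also stands: the 88–89% is a conservative figure. However, the sample size section treats missing patients as lost, which is why it adds an allowance at all, and it claims no recovery through the model.

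Three stronger readings are tempting, and the documents do not support them:

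- *That 41 was wrongly rounded down.* The pilot SD is printed as an integer. A value such as 13.96 gives 40.95 by the normal formula, so 41 could be correctly rounded up.
- *That the allowance was made by multiplying by 1.2 instead of dividing by 0.8.* No inflation formula is given. 41 × 1.2 = 49.2, rounded up to 50 per arm, would give 100, but so would choosing a round number near 102.5.
- *That 43 per arm and a 14% limit are the plan's true thresholds.* They follow only if the t-test is chosen. The protocol names no test, and the normal formula gives 42 per arm and 16%.

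**Conclusion.** The point holds as a minor inconsistency in stated figures. The claim that 100 recruits cover 20% missing data is wrong on the protocol's own numbers: 80 remain against 82 required, and the cover extends to 18%. This part needs no modelling assumption.

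The shortfall in power rests on an SD of exactly 14, equal arms, and a simple two-group comparison of completers. Under these assumptions 40 per arm gives 88.4% to 89.1%. An SD slightly below 14 or use of partial follow-up in the mixed model would narrow the gap. A reader might infer that the trial is materially underpowered; a loss of 0.9 to 1.6 percentage points does not support that.

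**What to change.** Reword the sample size section in one of two ways.

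- State that 100 patients with 20% missing leave 40 per arm, giving about 88–89% power for a 10-point difference with SD 14.
- Or keep the requirement of 82 and state that 100 recruits retain it for up to 18% missing. If the 90% figure is kept with the printed SD of 14, add that it holds up to 16% missing by the normal formula or 14% by the t-test, and name the method used.

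If the pilot SD was below 14 before rounding, print it to the precision used, so that the 41 can be reproduced. If the sponsor relies on the mixed model to make up the difference, the section should say so.

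The cost is wording only. No extra patients are needed, and the design and analysis do not change. The one downside is a slightly less favourable stated power or missing-data tolerance.

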### Analysis plan

The primary endpoint in this study is KOOS_4_ at 12-month follow-up. Results will be analysed by intention-to-treat (ITT) principle. However, data will also be analysed by per-protocol (PP) approach to account for protocol violations such as patients who were deemed not compliant to treatment or patients who underwent a surgical procedure of the knee due to treatment failure during the course of the study.

Descriptive frequency analysis will be used for baseline characteristics. For continuous variables, the mean and standard deviation will be reported and for categorical variables, the frequencies and percentages will be reported. Between-group comparisons of change from baseline to 1-year follow-up in the primary and secondary continuous outcomes will be analysed using a generalized linear mixed model (GLMM). Testing for normality of distributions of outcomes will be based both on the Shapiro-Wilks test and a visual analysis of the histogram plot. Categorical secondary outcomes will be analysed using the ordinal logistic regression function under GLMM. A two-sided *p*-value less than 0.05 will be considered as statistical significance. An analysis will be done on the nature of the missing data to determine if the data was missing at random or a systemic bias was present resulting the missing data.

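### The primary endpoint is a 12-month KOOS4 score but the comparison is of change from baseline, with no stated adjustment for baseline KOOS4 or gender; fixing the adjusted contrast would gain precision at no cost

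*Protocol article*

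**What the plan says.** Three places in Component 1 of the protocol article bear on the point.

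- **Analysis plan.** The endpoint is worded as a score: "The primary endpoint in this study is KOOS_4_ at 12-month follow-up". The comparison, by mixed model, is worded as a change: "Between-group comparisons of change from baseline to 1-year follow-up". No fixed effects, covariates or covariance structure are listed.
- **Randomization and concealment of allocation.** "Stratification is based on gender to ensure equal distribution in both groups". No other stratification factor is named.
- **Sample size calculation.** The trial needs 41 per arm to show a 10-point gap in KOOS4 with 90% power at a two-sided 0.05 level, assuming "a standard deviation of 14". On the source of these values it says: "The anticipated population KOOS_4_ and standard deviations were based on the initial pilot study". It does not state whether 14 is the SD of a KOOS4 score or of its change.

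Baseline data are collected before randomization (Trial procedure), and gender is among the Baseline measures, so both variables will be available.

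**The concern.** The endpoint and the sample size are worded in terms of a KOOS4 score, and the comparison in terms of a change in KOOS4. These describe the same expected treatment difference under randomization, but not the same variance. A plain change score uses the baseline only by subtraction, which in effect fixes its coefficient at 1. Regression on the baseline estimates that coefficient and so removes at least as much variance.

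Two things are at stake. The first is precision: an analyst who follows the sentence literally, with unadjusted change, may discard information that the trial already holds. The second is the link to the sample size: if 14 is the SD of a score, the change score has that same SD only at one particular baseline-to-12-month correlation, and the article gives no correlation. Little slack exists to absorb a loss, because 20% missing from 100 patients leaves 80, or 40 per arm, against the 41 per arm required.

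**Working it through.** **Inputs from the article:** difference 10, SD 14, two-sided alpha 0.05, power 90%, 41 per arm, 100 recruited, 20% missing, 1:1 allocation. **Assumed:** the baseline-to-12-month correlation rho (range 0.3 to 0.7), equal SDs at baseline and 12 months unless stated otherwise, and, for the power table, that 14 is the SD of the score.

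**1. The plan's own figure.** n per arm = 2 × (1.960 + 1.282)² × 14² / 10² = 41.2. This agrees with the stated 41 (42 when rounded up; 43 by the t-test). Power by the t-test is 89.2% at 41 per arm and 88.4% at 40 per arm.

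**2. Variances.** Let s0 and s1 be the baseline and 12-month SDs.

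- Change: s0² + s1² − 2·rho·s0·s1
- Baseline-adjusted: s1²(1 − rho²)
- Difference (change minus adjusted): (s0 − rho·s1)²

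The difference is a square, so it cannot be negative, whatever the two SDs are. With s0 = s1 = 14 the formulas reduce to SD(change) = 14√(2(1 − rho)), SD(adjusted) = 14√(1 − rho²), and adjusted variance / change variance = (1 + rho)/2.

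**3. Power at 40 per arm, difference 10, t-test, 14 taken as the score SD.**

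| rho (assumed) | SD of change | Power, change | SD adjusted | Power, adjusted | Variance ratio |
|---|---|---|---|---|---|
| 0.3 | 16.57 | 76% | 13.36 | 91% | 0.65 |
| 0.4 | 15.34 | 82% | 12.83 | 93% | 0.70 |
| 0.5 | 14.00 | 88% | 12.12 | 95% | 0.75 |
| 0.6 | 12.52 | 94% | 11.20 | 98% | 0.80 |
| 0.7 | 10.84 | 98% | 10.00 | 99% | 0.85 |

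At rho = 0.5 the change score has exactly the planning SD, and its 88% is simply the power of the plan at 40 per arm. Below 0.5 the change analysis falls clearly short of 90%. At 0.6 and above it exceeds 90%.

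**4. If 14 is instead the SD of change.** The sample size then matches an unadjusted change analysis. Adjustment would need 27, 31 or 36 per arm at rho 0.3, 0.5 and 0.7 (normal approximation), against 42 by the same method. The gain in precision remains, but there is no shortfall relative to plan.

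**5. Unequal SDs.** Entry requires KOOS4 of 75 or less, which may narrow the baseline SD. As an assumed illustration, take s0 = 11.2 and s1 = 14. At rho = 0.3, SD(change) = √(125.44 + 196 − 94.08) = 15.08, and power at 40 per arm is about 83% rather than 76%. The correlation at which the change SD equals 14 drops from 0.5 to 0.4. At rho = 0.8 the two analyses are equally precise, since 11.2 − 0.8 × 14 = 0.

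**6. Gender.** The article gives no figure relating gender to KOOS4, so the effect of including or omitting it cannot be calculated.

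**The case against.** The strongest reply is that a reader might infer that baseline KOOS4 and gender are left out of the model, and the article does not say so. It names a mixed model and lists no terms at all. Covariates are commonly left to the full protocol or the SAP, which are not shown. Moreover, with KOOS4 measured at baseline, 3, 6 and 12 months, a between-group comparison of change by mixed model is ordinary wording for a group-by-time contrast. A model with a common baseline mean estimates that contrast with about the efficiency of covariate adjustment, and a change-score model with baseline as a covariate gives the same treatment estimate as adjusting the 12-month score. This stands: exclusion is not established, and precision is lost only with an unadjusted change score or with free baseline means in each arm.

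A reader might also infer that the SD of 14 is wrong for the analysis, or that the trial is underpowered. Neither is shown. The wording about the pilot study leans towards a score SD but is not explicit, no correlation is given, and the table shows power above 90% at rho 0.6 or more. The 76% is one case that depends on rho, on equal SDs and on a score SD.

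Finally, an unadjusted comparison of change in a randomized trial is valid, and omitting a stratification factor that predicts the outcome makes intervals conservative rather than too narrow. That also stands, and it limits the point to precision and clarity. What the reply does not remove is the stated mixture of a 12-month score as endpoint, a change as comparison and an SD of unstated type.

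**Conclusion.** The point holds as a request to fix the primary contrast, not as an error that invalidates the analysis. The article words the endpoint as a score and the comparison as a change, and describes no adjustment for baseline KOOS4 or gender. An unadjusted change contrast is never more precise than a baseline-adjusted one, for any pair of SDs. The size of the gain depends on assumptions: with equal SDs the adjusted variance is 65% to 85% of the change-score variance for rho from 0.3 to 0.7. A clear shortfall below 90% power is possible only if the analysis is unadjusted, 14 is the SD of the score and, with equal SDs, rho is below 0.5. The contribution of gender cannot be quantified. No bias or inflation of the type I error is claimed.

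**What to change.** In the Analysis plan, define the primary estimate as the between-group difference in KOOS4 at 12 months from the mixed model, with baseline KOOS4 and gender as fixed covariates. An equivalent choice is a repeated-measures model with a common baseline mean in the two arms, plus gender. Use the same form for the secondary continuous outcomes that are measured at baseline. In the Sample size calculation, state whether the SD of 14 is of the KOOS4 score or of its change and, if it is of the score, give the baseline-to-12-month correlation from the pilot where available.

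The cost is wording only. Both covariates are already collected, and neither the sample size nor the visit schedule changes.
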